## Background

IgE-mediated food allergy is a burden in industrialized countries with up to 8% of all infants and children suffering from this condition [1]. Especially infants with eczema are at high risk for developing food allergies [2]. About half of these children become sensitized and about one third will develop clinically relevant food allergy [1, 3, 4]. The main elicitors are HE, CM, PN and tree nuts. Food allergy often starts in infancy and interestingly the children become sensitized against certain foods even before eating them for the first time. It is the current understanding that sensitization occurs via the cutaneous route due to an impaired skin barrier function in these infants [2]. In the past, prevention strategies concerning the development of food allergy have been driven by avoidance of allergenic foods in high-risk infants. Despite these attempts, a rising prevalence of food allergy has been observed [1, 5]. Therefore, current guidelines no longer recommend avoidance [6, 7]. However, the optimal way of allergen introduction into the infants´ diet is still under debate. The main questions are “when,” “how,” “which allergen,” and “which children.”

To address these questions, several randomized controlled studies have been conducted with different foods [8–14]. The LEAP trial in the UK focused on peanut allergy in high-risk children (severe eczema and/or hen’s egg allergy) [8]. After randomization, 540 participants from 4 to 11 months of age were asked to consume peanut three times weekly or to avoid peanut strictly until the age of 5 years. In this high risk population, early and continuous feeding of peanut products reduced the development of peanut allergy by 80% [8]. However, it is still unclear how these results can be transferred to other countries where peanuts are less frequently consumed. For instance, data from Singapore showed very low prevalence rates of peanut allergy despite the fact that peanuts are not introduced into infants’ diets in the first year of life [9].

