Supplies of study product will be dispensed at each visit. Parents will be instructed to contact the study site in case of an immediate type allergic reaction after food exposure (either to the study product or due to exposure to any food allergens). Additionally, in case of recurrent gastrointestinal symptoms, worsening of eczema or any suspected adverse event parents are asked to contact the study site. Two weeks after V1, parents will be called (phone call 1; PC1) to investigate compliance and tolerability of the study product and to promote retention. Subjects will be required to visit the study site after 6 (V2), 12 (V3) and 18 (V4) weeks, and 6 (V5) months of intervention. At V2, V3, V4, and V5, information on medical history, medication (especially treatment of eczema), and nutrition (breast feeding, complementary foods) will be recorded. In addition, anthropometric measurements and a physical examination including SCORAD and EASI score will be performed. Stool, dust, skin swabs, and saliva samples will be collected. TEWL will be performed. At V2, V3, and V4, the first feeding of the next higher dose of the verum, respectively of the placebo in order to ensure blinding, will be performed at the study site. Supplies of study product will be dispensed at each visit. Two weeks after V2, V3, and V4, parents will be called (PC2, PC3, and PC4) to investigate compliance and tolerability of the study product. An additional blood sample from the participant and its mother will be collected, and a SPT with HE, CM, PN, and HN will be performed at V5 (all extracts including positive and negative controls: ALK Abelló, Germany). Participants sensitized to any of the checked foods (elevated food-specific IgE (> 0.1 kU/l) or positive SPT (wheel size > 3 mm)) will be invited to undergo an OFC at V6. Sensitized patients are instructed to continue consuming the study product until V6 will take place. OFC will be performed in a double-blinded, placebo-controlled manner in accordance with clinical routine practice of the Charité-Universitätsmedizin Berlin, based on PRACTALL international guidelines for OFC and stopped using standardized stopping criteria based on PRACTALL guidelines [23]. Roasted, defatted peanut flour, defatted HN flour, fresh CM, and pasteurized raw HE will be used for OFC. Up to seven increasing dose steps at 30-min intervals using a semi log scale ranging approximately from 2 mg to 3 g food protein (depending on the individual allergen) will be administered. In case of absence of any objective, allergic symptoms, a cumulative dose up to 4.5 g food protein will be administered on another day. In patients with allergic reactions to raw HE and fresh CM, an additional food challenge will be offered with baked HE or CM, respectively. Participants who developed a clinical relevant food allergy at the end of the trial will receive an individualized dietary counseling. Moreover, parents are offered to contact the outpatient clinic of the Department of Pediatric Pulmonology, Immunology and Critical Care Medicine, Charité – Universitätsmedizin Berlin, for further consultation. In case of discontinuation or deviation from the intervention protocol, all participants are encouraged to maintain the scheduled visits or phone calls and collection of all possible data is planned. For detailed description of all study procedures, see Table 2.

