### Sample size calculation

Analyzing 120 infants (80 in the active group and 40 in the placebo group) will result in at least 80% power to detect a difference in the primary endpoint (food allergy after 6–8 months of intervention) of 10% in the intervention group vs. 33% in the control group, based on a two-sided chi-squared test with significance level 5%. In order to compensate for a potential dropout-rate of about 20%, 150 infants will be randomized (100 infants to the active group and 50 infants to the placebo group). As the number of twins included to this study is expected to be very low (i.e., one or two pairs), the correlation due to twin status is not taken into account for the sample size calculation.

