### Statistical analysis

The primary analysis of the primary endpoint will be performed by logistic regression with (fixed) factor treatment group (active, placebo) taking the correlation of twins into account. From this model, the odds ratio for treatment will be calculated with 95% confidence interval and a *p*-value for the treatment group comparison. The analysis will be performed on the full analysis set (FAS) without imputation of missing values. The significance level will be set to 0.05 (two-sided). All other analysis will be considered explorative. Several explorative sensitivity analysis will be performed for the primary endpoint: a re-run of the primary analysis model without taking the correlation of twins into account and a re-run of the primary analysis model with the per- protocol population (instead of the FAS). In case of relevant differences between the treatment groups with respect to baseline variables, the primary analysis will be repeated with further adjustment variables (FAS population). Moreover, several subgroup analysis will be conducted regarding the following subgroups: carrier of mutations in the Filaggrin gene; infants with at least one parent with eczema; infants with at least one parent with atopic diseases (asthma, rhinoconjunctivitis, eczema); breastfed children/formula fed children, children with impaired skin barrier function (measured with TEWL); and household allergen exposure. Subgroup analysis will be performed by additionally including the subgroup variable and the interaction term (subgroup*treatment group) into the primary analysis model (FAS population). In case subpopulations regarding to the consumption of CM exist, these subpopulations will be analyzed separately (FAS population).

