Explorative analysis of secondary endpoints will follow the same principle as the primary analysis of the primary endpoint, i.e., models with (fixed) factor treatment group, taking the correlation of twins into account. Binary endpoints will be analyzed by logistic regression; continuous endpoints will be analyzed by analysis of covariance (ANCOVA) with the respective baseline value (if available) as additional covariate. Secondary endpoints will be analyzed with the FAS; selected secondary endpoints will also be analyzed with the per-protocol population. Concerning safety endpoints, the nature, frequency, and severity of adverse events and safety variables, including serious adverse events, will be summarized descriptively by treatment group. As a general strategy, missing data will not be imputed in this study. No interim analyses for efficacy are planned.

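### The eczema, topical-treatment and wheezing endpoints at the food challenge compare only infants sensitised at V5, so the arms compared there are not the randomised groups

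*Protocol article*

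**What the plan says.** Secondary endpoints (protocol article) lists four outcomes on the same schedule: change in SCORAD, change in EASI, change in topical eczema treatment, and wheezing. Each is assessed at 6, 12 and 18 weeks and at 6 months (V2 to V5). Each is assessed once more at the oral food challenge (V6), where the list limits it to infants sensitised at the 6-month visit.

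Study procedures explains the limit. Infants with raised food-specific IgE or a positive skin prick test at V5 "will be invited to undergo an OFC at V6". For the others the intervention stops at that point (legend of Fig. 1).

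Statistical analysis says that secondary endpoints follow the principle of the primary analysis, that is, "models with (fixed) factor treatment group, taking the correlation of twins into account". Binary endpoints get logistic regression, and "continuous endpoints will be analyzed by analysis of covariance (ANCOVA) with the respective baseline value (if available) as additional covariate". On missing values: "As a general strategy, missing data will not be imputed in this study". No secondary endpoint or time point is taken out of the between-arm model. The same section gives the status of everything beyond the primary analysis: "All other analysis will be considered explorative".

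**The concern.** A between-arm comparison is protected by randomisation when the infants compared are those randomised, or a subset fixed before treatment began. Sensitisation at V5 is neither. It is measured after about 6 months of product, and allergen-specific IgE at that time is itself listed as a secondary endpoint, so the trial is looking for a product effect on it.

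The Background also ties selection to the outcome being compared. It attributes sensitisation to the cutaneous route through an impaired skin barrier, so infants with worse eczema may be more likely to be sensitised and to reach V6. If the product changes who becomes sensitised, the two V6 groups can differ in eczema severity even if the product does nothing to eczema. In the direction the trial hopes for (less sensitisation on active), the active infants who remain sensitised are the more strongly predisposed ones, and the product would look worse for eczema than it is. If it raised sensitisation, the sign would reverse.

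The impact on eczema severity is a stated secondary objective and the Discussion returns to it, so a V6 result is likely to be read.

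**Working it through.** **Inputs from the protocol article**
- "Analyzing 120 infants (80 in the active group and 40 in the placebo group"), from Sample size calculation. With about 20% dropout, 120 / (1 - 0.20) = 150 randomised, as stated. No SD, correlation or power is given for SCORAD or EASI.
- Background sensitisation, from Background: "About half of these children become sensitized and about one third will develop clinically relevant food allergy". I use P0 = 0.50 for placebo.

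**Assumed, because the document gives no figure**
- Sensitised share on active, P1: 0.35 or 0.25.
- Correlation r of eczema severity with the liability to be sensitised, the same at baseline and V6: 0.4 or 0.6.
- Correlation of baseline with V6 score: 0.6.
- No true effect of the product on eczema.

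**Numbers at V6.** Placebo: 40 x 0.50 = 20. Active: 80 x 0.50 = 40 with no effect on sensitisation, 80 x 0.35 = 28, or 80 x 0.25 = 20.

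**Step 1: raw shift.** With normal liability, the mean liability among the sensitised is m = phi(z)/P, where z cuts off the upper share P.
- P = 0.50: m = 0.798
- P = 0.35: m = 1.058
- P = 0.25: m = 1.271

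The raw difference in severity is r x (m1 - m0):
- 35% vs 50%, r = 0.4: 0.4 x 0.260 = 0.10 SD
- 35% vs 50%, r = 0.6: 0.6 x 0.260 = 0.16 SD
- 25% vs 50%, r = 0.4: 0.4 x 0.473 = 0.19 SD

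**Step 2: the planned baseline adjustment.** Selection shifts the baseline score by the same amount, so ANCOVA removes part of the difference. Within the sensitised, the slope on baseline is b = (0.6 - r² k) / (1 - r² k), with k = m(m - z) averaged over the two groups (about 0.68 for 35% vs 50%, 0.70 for 25% vs 50%). The adjusted difference is the raw difference times (1 - b).

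| Sensitised, active vs placebo | r | Raw (SD) | b | Adjusted (SD) |
|---|---|---|---|---|
| 35% vs 50% | 0.4 | 0.10 | 0.55 | 0.05 |
| 35% vs 50% | 0.6 | 0.16 | 0.47 | 0.08 |
| 25% vs 50% | 0.4 | 0.19 | 0.55 | 0.09 |
| 50% vs 50% | either | 0 | n/a | 0 |

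A simulation of the first three rows gave the same adjusted values. The remaining corner, 25% vs 50% with r = 0.6, gives 0.6 x 0.473 = 0.284 raw, b = 0.47, and about 0.15 SD adjusted. An unadjusted difference in change scores would be about 0 throughout, because baseline and V6 shift equally under this model.

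**Step 3: against the noise.** With 20 placebo and 20 to 28 active infants, the ANCOVA standard error is about 0.22 to 0.25 SD. The three main scenarios are thus biased by roughly 0.2 to 0.4 standard errors, and the extreme corner by about 0.6 (0.15 / 0.24).

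**Step 4: would a repeated-measures model change V5?** Assume equal correlation rho between all visits and 5% of infants lost before each of V2 to V5, leaving 80% at V5. The variance of the V5 contrast, relative to an ANCOVA on those present at V5, is 0.987, 0.974 and 0.963 for rho = 0.3, 0.5 and 0.7, a gain of about 1 to 4%.

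**The case against.** **The restriction is openly stated and the endpoints are exploratory.** Both are true. Neither the primary conclusion nor the sample size depends on V6 eczema scores, and V2 to V5 already covers the scheduled 6 months in all infants. This limits the consequence. It does not turn the V6 comparison into a randomised one, and the analysis text does not set V6 apart.

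**Baseline adjustment deals with it.** Partly. It roughly halves the raw shift, which is why the adjusted figures are the ones to cite. It does not remove the shift, because baseline severity does not carry all the information that sensitisation at V5 carries about severity at V6.

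**The product may not change sensitisation.** Then the shift in this model is zero. The design assumption for the primary endpoint, "10% in the intervention group vs. 33% in the control group", concerns food allergy, so it does not settle what happens to sensitisation.

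**A stronger reading that the document does not support.** A reader might infer that SCORAD and EASI are analysed by separate complete-case ANCOVAs at each visit, wasting the repeated data and biasing V2 to V5. That goes too far:
- The article names ANCOVA once, for all continuous secondary endpoints. It is an abridged protocol, and how several visits are modelled is commonly left to the full protocol or SAP, which are not shown.
- A baseline-adjusted ANCOVA at any of V2 to V5 is a valid randomised comparison if missingness is ignorable given baseline.
- At V5 the precision gain from a repeated-measures model is only the 1 to 4% above. A large gain appears only for an effect averaged over V2 to V5, which is a different quantity and pools four dose steps (Table 1).
- Bias from dropout that depends on intermediate scores is possible, but nothing in the document allows it to be sized. Participants who stop the product are encouraged to keep attending.

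**Conclusion.** The point holds for V6 only, and it is minor. As written, the plan makes between-arm comparisons of SCORAD, EASI, topical treatment and wheezing in a group selected by a post-randomisation status that the product may change.

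For the two scores, the planned ANCOVA would show a spurious difference of about 0.05 to 0.09 SD in the three main scenarios, about 0.15 SD in the most extreme combination of the same assumptions, and nothing if sensitisation is equal in both arms. The active-arm sensitisation rates and all correlations are assumed, so these figures show an order of magnitude and do not predict the trial's result. The direction follows the effect on sensitisation: fewer sensitised infants on active makes the product look worse for eczema. No size was worked out for topical treatment or wheezing, where the same argument applies in kind.

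**What to change.** Base the between-arm comparisons of SCORAD, EASI, topical treatment and wheezing on V2 to V5 in all infants, and name V5 as the main time point. Present V6 values by group descriptively, with no between-arm test, and say why: only infants sensitised at V5 attend.

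Optionally, analyse V2 to V5 for each score in one repeated-measures model with baseline, treatment, visit, treatment by visit, an unstructured within-child covariance and the twin-pair correlation already planned. This uses the partial data of infants who drop out and allows for dropout that depends on earlier observed scores, but little precision should be expected from it at V5. V6 should stay out of that model, because whether a V6 value exists depends on sensitisation, which the model does not contain.

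The cost is two or three sentences in the analysis plan, plus a little programming if the optional model is adopted. No new data and no change in sample size are needed.

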## Discussion

This clinical trial, including 150 infants with eczema at 4–8 months of age, will investigate whether an early introduction of baked HE, CM, PN, and HN can reduce the risk for developing food allergy in the first year of life.

The study population of this trial consists of infants with eczema, who are at risk for development of further atopic conditions, and therefore does not represent the general population. Interestingly, it has been reported that even in children with food allergy but without eczema, an impaired skin barrier function occurs [24]. One third of the infants taking part in our HEAP study, who were sensitized against HE, had no atopic dermatitis at the screening visit [10]. Nevertheless, Natsume et al. were able to show that the introduction of small amounts of heated HE is particularly effective in infants with atopic dermatitis that might already be sensitized [13]. It needs to be shown, whether this finding can be confirmed and whether this approach is suitable for other food allergens. Besides the introduction of HE, Natsume et al. treated participants’ eczema attentively throughout the whole study period. In our trial, the treatment of the subjects’ eczema will not be part of the study intervention. However, during the interventional period of our study treatment of eczema will be assessed and the impact of an early introduction of small amounts of allergenic foods in regard to severity of eczema will be evaluated. Severity grading will be performed by using different objective and standardized diagnostic systems (POEM, SCORAD, and EASI diagnostic score).

Since many children seem to develop food allergy to more than one food [14, 25], a further strength of our study is that we introduce multiple food allergens at the same time, while keeping the study procedures for the participants as simple as possible. Although it was not feasible to integrate all common food allergens in our interventional product, it does contain the most important ones (HE, CM, PN, and HN). Recently, Skjerven et al. evaluated the early and regular use of skin care and the early complementary feeding of PN, CM, HE, and wheat (WT) at 3–4 months of age in the general infant population. Participants were randomized to either a skin intervention, a food intervention, a combined intervention or a no intervention group. The food intervention group was instructed to introduce PN at 3–4 months of age, followed by CM 1 week later, WT the next week, and finally HE in the fourth week. The infants´ parents were advised to administer each of the foods from the finger or from a teaspoon at least 4 days per week. Although the final results have not been published yet, Skjerven and colleagues reported that the adherence to the food intervention was quite low (32%) [26]. This observation and the results of the EAT study underline that the introduction of food allergens has to be suitable for real life settings at this very young age, in order to guarantee compliance [14, 26].

In case of sensitization against certain foods, determined at the end of the interventional period, OFC will be performed in a double-blinded, placebo-controlled manner, representing the gold standard procedure in diagnosing food allergy.

Within this study, one of our aims is to assess the safety of an early introduction of small amounts of allergenic foods in infants with eczema in the first year of life regarding the occurrence of immediate type allergic reactions, gastrointestinal symptoms, and growth. Currently, children with moderate to severe eczema are routinely screened for sensitization against the most important food allergens [27]. In order to avoid anaphylactic reactions occurring at home within the first feeding, screening for sensitization against certain food allergens needs to be conducted before these foods are introduced into the infant´s diet [27]. The results of this trial will help to clarify, if an early introduction of potentially allergenic foods in high-risk infants can be done safely by starting from a very small dose and increasing the amount in a stepwise manner, even without screening for sensitization before.

The results of the trial will be submitted for publication in peer-reviewed journals and will further be communicated to participants, health care providers, and professional groups including health visitors and midwives, as they may affect current dietary recommendations regarding the prevention of food allergy.

## Trial status

This is an abridged protocol based on protocol version 4.0 dated 05 April 2021.

The first patient was randomized in February 2020, and the last patient is planned to be enrolled in February 2023.

## Data Availability

All data generated in the CRU will be curated and organized into a set of files, shared on an online, publicly available data repository after peer-reviewed publication (preservation and accessibility of the data) to ensure potential secondary analyses, long-term archiving, and reuse by other researchers (scientific recognition). Besides the study protocol, publications are planned for the results in peer-reviewed journals. In addition, results will be communicated in lay language to participants and health care providers as they may affect current food prevention guidelines.

## Abbreviations

AE: Adverse event
ANCOVA: Analysis of covariance
BIH: Berlin Institute of Health
CRF: Case report form
CRU: Clinical research unit
DBPCFC: Double-blind placebo-controlled food challenge
DFG: German Research Foundation
EASI-Score: Eczema Area and Severity Index Score
EAT study: Enquiring About Tolerance study
eCRF: Electronic case report form
FAS: Full analysis set
HEAP trial: Hen´s Egg Allergy Prevention Trial
IgE: Immunoglobulin E
IgG4: Immunoglobulin G4
LEAP trial: Learning Early About Peanut trial
OFC: Oral food challenge
PC: Phone call
PP: Per Protocol
PRACTALL: PRACTical issus of ALLergology, Joint United States/European Union Initiative
REDCap: Research Electronic Data Capture
RNA: Ribonucleic acid
SAE: Serious adverse event
SAP: Statistical analysis plan
SCORAD: SCORing Atopic Dermatits
SPT: Skin prick test
TEFFA: Tolerance induction through early feeding to prevent food allergy in infants with eczema
TEWL: Transepidermal water loss
UK: United Kingdom
V: Visit
